## 2) Inventory Management of Investigational Products

- The principal investigator must ensure that the investigational products are correctly received by the pharmacist and stored in a secure location, and is responsible for preserving the products from damage before dispensing. The investigational products used in this study will not be used for any purpose other than the clinical trial.
- The principal investigator and the institutional pharmacist at the respective clinical trial site are responsible for the management of the investigational products.

- Investigational products will be stored separately in a locked storage area within the clinical pharmacy. During the pharmacist's absence, the storage area will remain locked to restrict access by individuals not involved in this clinical trial. However, if it is necessary for a subject to receive the investigational product or for a remaining product to be returned to the pharmacy in the pharmacist's unavoidable absence, a delegated investigator (with a medical license) may perform these duties.
- The investigational products must be stored in the clinical pharmacy of the study site in accordance with the clinical trial protocol, Investigator's Brochure (IB), and the Clinical Trial Management Guidelines. The pharmacist must check the storage conditions, expiration date, quantity, and storage status of the investigational products, and must record the measured temperature on a temperature log, which will be kept for record-keeping.
- When dispensing the investigational products to subjects, the pharmacist will complete the product inventory log and the subject-specific dispensing log. If any investigational product is returned by a subject, the details will be recorded in the subject-specific dispensing log.

#### **8.4. Return and Disposal**

- 1) In the event of a clinical trial being suspended or terminated, or if the investigator fails to conduct the trial in accordance with the protocol, unused investigational products will be recalled and disposed of.
  - Criteria for return and disposal:
    - When the expiration date of the investigational product has passed.
    - Unused investigational products after the clinical trial is completed.
    - When there are abnormalities in the contents or packaging.
- 2) Return of Unused Investigational Products
  - When a subject wishes to return unused investigational products, the quantity and condition of the returned products will be verified and handed over to the pharmacist. The pharmacist will record the details in the subject-specific dispensing log.
- 3) Disposal of Investigational Products after Trial Completion
  - Unused investigational products will be recalled by the manufacturer and disposed of according to the manufacturer's internal regulations and disposal guidelines.
  - The institutional pharmacist, in consultation with the Principal Investigator, must return the unused investigational products and keep the return receipt and relevant disposal confirmation documents.
  - However, if disposal through the manufacturer is not possible due to their circumstances, the products will be disposed of by the institution according to the drug disposal guidelines of the on-site hospital pharmacy. All records regarding the return and disposal must be created and retained.

## 9. Methods and Administration

### 9.1. Investigational Product Administration

The investigational product will be administered once per packet (1 pack) three times a day, before or between meals. The total administration period is a maximum of 7 days (21 packets). The daily dose for each group is as follows. If the cold symptoms disappear before the maximum 7-day administration period, subjects will stop taking the medication and return the remaining investigational products.

- ✓ Test Group (GGTCS): 1 packet (3g) per dose, 3 times/day, for a maximum of 7 days.
- ✓ Control Group (Placebo): 1 packet (3g) per dose, 3 times/day, for a maximum of 7 days.

### 9.2. Concomitant and Prohibited Medications

#### 1) Permissible Concomitant Medications

- Medications that subjects have been taking for 4 weeks prior to participating in the clinical trial and are not classified as prohibited drugs may be permitted at the investigator's discretion.
- Medications used for the transient treatment of other diseases will be co-administered after consultation with the investigator.
- Detailed information about all concomitant medications (including those for other diseases or for treating adverse events) will be recorded in the subject's Case Report Form (CRF), including the drug name, purpose of administration, dose, and duration.

#### 2) Prohibited Concomitant Medications

- During the clinical trial period, the use of the following medications that may affect symptoms is prohibited. If the use of a prohibited medication is necessary, the subject must discontinue the clinical trial.
  - ① Antibiotics, antiviral agents, steroids, decongestants, antihistamines, antitussives/expectorants, and other medications expected to relieve nasal congestion.
  - ② Medications administered for the same therapeutic purpose as the investigational product or those that may affect the improvement of nasal congestion symptoms.
  - ③ Medications containing the same active ingredients (Puerariae Radix, Ephedrae Herba, Zizyphi Fructus, Cinnamomi Ramulus, Paeoniae Radix, Glycyrrhizae Radix et Rhizoma, Zingiberis Rhizoma Crudus, Cnidii Rhizoma, and Magnoliae Flos), even if they are not used for the same therapeutic purpose as the investigational product.

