## **7. Dropout and Early Termination Criteria**

### **7.1. Dropout**

Dropout refers to the premature termination of a subject's participation before completing all study procedures. The investigator may stop the treatment and observation and withdraw the subject, and the subject may voluntarily withdraw from the study at any time. A subject who meets any of the following criteria may be withdrawn from the study at the discretion of the principal investigator or responsible investigator. In the event of any of the following, the administration of the study drug and the trial itself may be discontinued, leading to withdrawal.

- 1) If a subject is confirmed to violate the inclusion/exclusion criteria after screening.
- 2) If a systemic disease, not discovered during pre-administration screening, is found in the subject.

- 3) If the investigator determines that continuous administration is inappropriate due to a serious adverse event in the subject.
- 4) If the investigator determines that continuous administration is inappropriate due to the severity of an adverse event.
  - Subjects who discontinue early due to an adverse event may receive appropriate treatment for the event if necessary.
- 5) If the investigator determines that the subject's symptoms have worsened and other treatment is required.
- 6) If the subject or their legal representative withdraws consent for participation in the clinical trial or requests to stop the administration of the investigational product (due to unsatisfactory therapeutic effect during the trial period).
- 7) If the subject's visits and follow-up are not possible.
- 8) If the subject violates the clinical trial protocol or leaves the hospital without permission, making it difficult to continue the trial.
- 9) If the subject takes any prescribed medication or over-the-counter medication that could affect the study's outcome (e.g., safety, pharmacokinetic properties) without the supervising physician's instruction during the clinical trial period (all periods after screening).
- 10) If the subject's medication compliance is significantly low, at less than 70%.
- 11) Other cases where the investigator judges the continuation of the clinical trial to be inappropriate.

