The date, reason, and a summary of the dropout will be recorded on the Case Report Form (CRF) conclusion page. The investigator should make every effort to follow up with subjects who have dropped out or withdrawn from the trial. Subjects are not obligated to state the reason for their withdrawal. However, the investigator must record the reason for discontinuation or the failure to ascertain the reason in the CRF. For subjects who discontinue due to an adverse event, follow-up examinations will be conducted as deemed necessary by the investigator.

Withdrawn and dropped subjects will not be replaced with new subjects.

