## **7.2. Early Termination**

The principal investigator may prematurely terminate this clinical trial after discussion with the funding organization if any of the following situations, which require the discontinuation of the study, occur. If a subject is withdrawn from the study before drug administration, they will be considered a screening failure, and it is not mandatory to complete all assessments.

The criteria for early discontinuation of the clinical trial are as follows:

- 1) If an unexpected or unacceptable risk is discovered in the subjects.

- 2) If moderate or severe adverse events, judged to be related to the investigational product, occur in more than 25% of all subjects.
  - The severity of adverse events will be evaluated with reference to the National Cancer Institute (NCI) "Common Terminology Criteria for Adverse Events (CTCAE) version 4.0," and a decision will be made on whether to terminate the entire clinical trial.
  - If the study is judged to pose a risk to subjects based on the progression of the adverse event and the causal relationship with the study drug, the investigator will permanently discontinue the subject's treatment in this clinical trial.
  - For subjects who discontinue early due to an adverse event, the investigator or their designee will continue to evaluate the subject until the adverse event is resolved or judged to be permanent.
- 3) If all subjects have not been enrolled despite a sufficient recruitment period.

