### 9.3. Rescue Medication

Subjects are permitted to take Acetaminophen if they experience fever (38°C or higher) or extreme pain. However, the maximum dose is limited to 6 tablets/day and 18 tablets/week (500mg/tablet). Subjects who complain of a high fever of 39°C or higher will be withdrawn from the study.

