#### **10.2.5. Monitoring for Symptom Worsening**

If a subject's symptoms worsen during a visit or between visits, medical examinations and actions will be

taken. For subjects with a possibility of rapid symptom worsening, their condition will be checked by phone within 3 days after the visit. If a high fever or extreme pain occurs, the use of a rescue medication (Acetaminophen) is permitted. If the investigator determines that a prohibited concomitant medication is necessary, the study will be discontinued for that subject and the required medication will be provided.

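### Needing a prohibited medicine, or a fever of 39°C or higher, ends study participation, and no Day 7 or exit WURSS-21-K or diary return is required afterwards

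*Protocol*

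**What the plan says.** Three places in the protocol turn a clinical trigger into an exit from the study.

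- Section 9.2, on prohibited medicines: "If the use of a prohibited medication is necessary, the subject must discontinue the clinical trial". The stated reason is that "the use of the following medications that may affect symptoms is prohibited".
- Section 10.2.5, when the investigator finds such a medicine necessary: "the study will be discontinued for that subject and the required medication will be provided".
- Section 9.3: "Subjects who complain of a high fever of 39°C or higher will be withdrawn from the study".

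Section 7.1 is softer. Subjects meeting its criteria "may be withdrawn from the study at the discretion of the principal investigator or responsible investigator". Item 5 (worsening that needs other treatment) and item 9 (taking a medicine that could affect the outcome without the physician's instruction) overlap the prohibited-medicine trigger. No listed item in 7.1 corresponds to the 39°C rule. Section 7.1 also pairs the two kinds of stopping: "The investigator may stop the treatment and observation and withdraw the subject".

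On what follows an exit, 7.1 states: "The investigator should make every effort to follow up with subjects who have dropped out or withdrawn from the trial". It names no measure, time point or diary.

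The primary endpoint is the change in WURSS-21-K total score from baseline to Day 7. Between Visits 2 and 3 the scheduled scores are kept in the subject's diary, which section 10.3.1.1 says is collected at Visit 3. Section 11.1.3 fills missing efficacy values in the FAS by LOCF.

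**The concern.** Both triggers plausibly mark subjects whose cold is going badly, so the Day 7 scores lost through them may be related to outcome. By contrast, under sections 9.1 and 9.4 a subject whose cold resolves stops the product, and nothing there calls for withdrawal. The plan thus already separates stopping the product from leaving the study, but only for those doing well.

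The illness is self-limiting and placebo subjects in the earlier studies changed by 29.09 points, so an early score carried forward may lie far from the Day 7 value. If the diary is not recovered there may be no post-baseline score at all. A later statistical analysis plan can change the imputation, but it cannot restore scores that the protocol did not have collected.

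**Working it through.** **1. The plan's own figure.** Inputs from section 5.3: difference 10, SD 21, two-sided 5%, power 80%, dropout 20%. n = 2 × (z₀.₉₇₅ + z₀.₈₀)² × 21² / 10² = 69.227, rounded up to 70 per group. 70 / 0.80 = 87.5, rounded up to 88, or 176 in total. The stated 70, 88 and 176 reproduce; this point challenges no figure.

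**2. Every clause that could require an efficacy score after exit.**

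| Protocol section | What it requires | WURSS-21-K or diary after withdrawal? |
|---|---|---|
| 7.1 | Date, reason and summary on the CRF; effort to follow up | Not named |
| 7.2 | For AE discontinuers, "the investigator or their designee will continue to evaluate the subject until the adverse event is resolved or judged to be permanent" | No; safety purpose |
| 7.2 | Full assessments waived for withdrawal before dosing | No rule given for withdrawal after dosing |
| 9.4 | Subjects bring the completed diary to the visit | Withdrawn subjects not addressed |
| 10.1 | Dropout status check at Visit 3 | No stated efficacy content |
| 10.2.4 | Additional visits: medicines, AEs, vital signs, optional laboratory tests | No |
| 10.3.1.1 | Diary collected at Visit 3 | No collection point for those who leave earlier |
| 10.6.4 | Termination for an AE: AE report and final laboratory test | No |

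None requires a Day 7 or exit score, or return of the diary.

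**3. What happens to such a subject in the analysis.** With diary pages recovered, LOCF carries the last score to Day 7. Without them, the two FAS definitions differ. The Synopsis (Statistical Analysis) requires at least one post-baseline efficacy measurement, so the subject leaves the FAS. Section 11.1.1 requires only that efficacy data were collected at least once, and excludes those with no data after screening. The Visit 2 WURSS-21-K is taken after screening, so under that wording the subject may stay in.

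**4. Illustration of size.** All rates and errors here are assumptions; the protocol gives none. Let d be the difference between arms in the proportion lost and e the mean error per lost subject. Shift = d × e.

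- d = 0 with equal e: shift 0.
- d = 0.05 (0.05 × 88 = 4.4 subjects): e = 5 gives 0.25; e = 10 gives 0.50; e = 20 gives 1.00 points.
- Relative to the 10-point design difference: 2.5%, 5% and 10%.
- SE of the difference = 21 × √(2/88) = 3.17, so the shifts are 0.08, 0.16 and 0.32 SE.

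**5. A harsher illustration.** Assume the carried-forward change is 0, and that without exit these subjects would have had their arm's mean change (39.09 against 29.09, a true difference of 10).

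- Equal exits of 10%: 0.90 × 10 = 9.0 (power 81% with 88 per group). Equal exits of 20%: 0.80 × 10 = 8.0 (power 72%).
- Exits of 5% on GGTCS and 15% on placebo: 0.95 × 39.09 − 0.85 × 29.09 = 12.4. Exits of 10% and 20%: 0.90 × 39.09 − 0.80 × 29.09 = 11.9.

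Equal exits shrink the difference and excess placebo exits enlarge it, so the direction depends on inputs that the protocol does not supply.

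**The case against.** The strongest reply has four parts.

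*Exit may not be truly mandatory.* Section 7.1 items 5 and 9 make overlapping exits discretionary, and 10.2.5 depends on the investigator's judgement that a prohibited medicine is needed. This stands as an inconsistency. It does not remove the point: 9.2 and 10.2.5 are the specific rules and are worded as obligations, and the 39°C rule has no listed counterpart in 7.1.

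*Follow-up is already asked for.* The duty in 7.1 covers all withdrawn subjects, not only AE cases, and 10.2.5 calls for examination when symptoms worsen, so the site will often be in contact. A reader might infer that the protocol bars withdrawn subjects from attending Visit 3 or handing in the diary. It does not; the gap is that neither is required.

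*The triggers may be rare.* Acetaminophen is allowed for fever of 38°C or higher or extreme pain, and cough or sore throat with sudden fever above 38°C is excluded at entry (section 5.2). Both may reduce exits, but no rate is given.

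*Scores under other medication answer a different question.* If the sponsor wants the effect without such medicines, later scores may not enter the primary analysis. That is fair, and it is why they must be flagged. It is a reason to stop the product and mark later scores, not to stop collecting them. The diary pages before exit and a score at exit are useful under either choice, and neither is required now.

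**Conclusion.** The point holds as a design weakness that should be corrected. For two triggers the stated rule is exit from the study, and no efficacy capture is required afterwards. For the prohibited-medicine trigger the protocol is also inconsistent with 7.1.

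Two stronger readings are tempting and unsupported. One is that the result will be biased in favour of GGTCS: the document gives no trigger frequency, so the number affected and the size and direction of any bias cannot be derived, and the shift is zero if loss and error are equal across arms. The other is that subjects without a recovered diary always drop out of the FAS: that follows from the Synopsis definition but not clearly from section 11.1.1.

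On assumed inputs the shift is 0.25 to 1.0 points (0.08 to 0.32 SE) for a 5-percentage-point imbalance, and larger under the harsher assumptions. How much of the planned 20% dropout would come from these triggers is unknown.

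**What to change.** - In 9.2, 9.3 and 10.2.5, replace exit from the trial with discontinuation of the investigational product. Keep the clinical triggers unchanged. Align 7.1 items 5 and 9.
- State that after product discontinuation a needed prohibited medicine is allowed, is recorded with its start date, and is not a further ground for exit. Without this, the ban in 9.2 would make such subjects continuing violators.
- At product discontinuation, administer the WURSS-21-K and check or copy the completed diary pages for every such subject, since later non-attendance cannot be known at that time.
- Then continue the diary to Day 7 and hold Visit 3, remotely if needed, unless the subject withdraws consent for follow-up or follow-up is not possible (7.1 items 6 and 7).
- Before unblinding, fix whether scores taken under other medication enter the primary analysis or a sensitivity analysis.

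The cost is protocol and consent wording, site training and one extra questionnaire at product discontinuation. The diary, Visit 3 and the instruments already exist, and the sample size stays at 176. The downside is that some Day 7 scores will be taken under other medication and must be flagged.

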### 9.3. Rescue Medication

Subjects are permitted to take Acetaminophen if they experience fever (38°C or higher) or extreme pain. However, the maximum dose is limited to 6 tablets/day and 18 tablets/week (500mg/tablet). Subjects who complain of a high fever of 39°C or higher will be withdrawn from the study.

#### 9.4. Compliance Assessment

To assess medication compliance with the investigational product, the number of doses taken and returned will be checked. Subjects should bring the empty packets and any unconsumed medication from the previous visit, along with their completed cold diary. The investigator will confirm whether the subject took the provided medication and will instruct them to return any remaining medication at the visit, and to avoid overdosing or losing the product. Medication compliance (%) will be calculated as shown below, recorded in the CRF to one decimal place. Compliance of 70% or more is considered "acceptable".

$$\text{Compliance (\%)} = \frac{\text{Number of investigational products actually taken}}{\text{Number of investigational products that should have been taken}} \times 100$$

When calculating the number of investigational products that should have been taken, the rule is to start taking the medication on the evening of the prescription date and to continue taking it until the evening before the next visit. The compliance will be calculated based on the amount that should have been taken and the amount actually taken from the evening of the prescription date until the evening before the next visit. If the subject stops taking the medication due to symptom resolution, compliance will be calculated based on the amount taken from the evening of the prescription date until the evening of the day before the symptoms resolved.

Subjects with a final medication compliance of less than 70% will be excluded from the PP analysis.

### 10. Procedure

#### 10.1. Timetable

|                    | Visit 1
(Screening  ) | Visit 2
(Baseline) | Visit 3  |
|--------------------|--------------------------------------|-----------------------|----------|
| Visit window       | Day -1~0                             | Day 0                 | Day 7-10 |
| Written Consent    | X                                    |                       |          |
| Demographic Survey | X                                    |                       |          |

X: All participants, △: If considered necessary by the investigator

 Screening test should be conducted within one day before Visit 2 and the results of clinical laboratory test should be able to be checked at Visit 2.

|                                                               |                                 |   |       |   |
|---------------------------------------------------------------|---------------------------------|---|-------|---|
| Medical History                                               |                                 | X |       |   |
| Physical Exam                                                 |                                 | X |       |   |
| Vital Signs                                                   |                                 | X | X     | X |
| Physical Measurements                                         |                                 | X |       |   |
| Laboratory Test                                   |                                 | X |       | X |
| Pregnancy Test                                    |                                 | △ |       |   |
| EKG                                                           |                                 | X |       |   |
| Chest X-ray                                                   |                                 | △ |       |   |
| PNS (Paranasal Sinuses) X-ray                                 |                                 | △ |       |   |
| Pattern Identification for Common Cold Questionnaire          |                                 | X |       |   |
| Inclusion and Exclusion Criteria Evaluation                   |                                 | X |       |   |
| Random Assignment                                             |                                 |   | X     |   |
| Administration of Investigational Product                     |                                 |   | Daily |   |
| Assessments                                                   | Nasal Congestion Severity Score | X | Daily |   |
|                                                               |                                 |   | X     | X |
|                                                               | WURSS-21-K                      |   | Daily |   |
|                                                               |                                 |   | X     | X |
|                                                               | Nasal Symptom Score VAS         |   | Daily |   |
|                                                               |                                 |   | X     | X |
|                                                               | Systemic Symptom Score VAS      |   | Daily |   |
|                                                               |                                 |   | X     | X |
|                                                               | Duration of Common Cold         |   | Daily |   |
|                                                               |                                 |   |       | X |
|                                                               | Recovery of Common Cold         |   |       | X |
|                                                               | Global Evaluation of Efficacy   |   |       | X |
|                                                               | EQ-5D-5L                        |   | X     | X |
| Prescription and Delivery of Assigned Investigational Product |                                 |   | X     |   |
| Distribution and Instruction for Common Cold Dairy            |                                 |   | X     |   |
| Compliance Test                                               |                                 |   |       | X |
| Common Cold Dairy Check                                       |                                 |   |       | X |
| Combined Medication Evaluation                                |                                 |   | X     | X |

 CBC (erythrocyte count, leukocyte count, hemoglobin, and hematocrit); LFT (AST, ALT, BUN, creatinine, and glucose).

 If pregnancy status is uncertain, urine hCG test for pregnancy confirmation following will be conducted, and the result must be negative.

|                             |   |   |   |
|-----------------------------|---|---|---|
| Dropout Status Check        |   | X | X |
| Adverse Reaction Evaluation |   | X | X |
| Instruction for Visit       | X | X |   |
| Completion of Trial Check   |   |   | X |

